#### Overview

Using the data generated in aims 1 and 2, SEM was used to evaluate the associations between framework elements in each domain. Identified associations were further evaluated in a large national administrative claims database.

#### SEM Analysis

The primary goal of aim 3 was to combine the results from aims 1 and 2 and extend these by building a statistical model that synergistically integrated the three domains of the UPOU conceptual framework. The UPOU framework has a number of complexities that limit the use of regression including multiple correlated predictors and outcomes, unobserved constructs that are difficult to directly measure, and nesting of patients with clinicians who are nested within sites. SEM can estimate latent variables and include them as both exogenous and endogenous variables in the same model, use multiple observable and quantifiable indicators to estimate latent variables from the shared variability of these indicators, and accommodate multiple endogenous variables (ie, dependent variables or outcomes) in 1 model. Multilevel SEM can estimate latent variables at 1 or more levels (eg, patient and clinician levels) and appropriately test associations at and across these different levels for categorical and continuous outcomes.

The SEMs were developed in several steps. The number of measurement models were estimated for all constructs that potentially used latent variables. Descriptive statistics were examined including means, medians, SDs, ranges, measures of central tendencies, and normality of the distributions. Extensive preliminary analyses were conducted to evaluate possible inconsistencies in the data, outliers, and variations in the data, and clinically and statistically relevant cutoff points that may facilitate the analyses were identified. The primary outcome measure was UPOU, measured as a dichotomous variable of cases and time-matched controls. The predictors of interest were grouped into 3 domains: patient characteristics, practice environment, and clinician characteristics. Each of these domains contained a number of directly observable and directly unobservable constructs. Examples of directly observable variables in the patient characteristic domain included age, sex, and employment status. Examples of directly unobservable constructs in the patient characteristic domain included symptoms of opioid withdrawal, opioid craving, and the psychosocial impact of chronic pain. Analyses (eg, coefficient α, principal components analysis, and factor analysis) were conducted to determine how to optimally combine scale items into reliable measures.

After all measurement models were established, a comprehensive structural model describing the conceptual framework was developed. In the first step, models were fitted separately by domain. For example, a parsimonious model relating patient characteristics to UPOU was developed. This first step involved a model-testing approach to trim a saturated model containing all patient-level constructs to develop a final parsimonious model that maximally explained UPOU with the least number of parameters. The results from aim 1 analysis directly informed this stage, but models varied due to the use of latent variables and a different statistical model. The Akaike information criterion, Bayesian information criterion, and the root mean square error of approximation were used to guide decision model trimming and refinement. This process was conducted separately for all 3 domains. The second step combined the parsimonious, domain-specific models into an integrated model. This involved multilevel SEM with a patient-level outcome (eg, UPOU) and predictors at the patient level, the clinician level, and the practice environment level. This model started with the 3 parsimonious, domain-specific models but then was expanded to test for possible cross-level interactions. For example, the effects of pain management training on UPOU varied by patient age. The conceptual model, previous research, and empirical findings were used to guide the model-building process, particularly with regard to the direction of association and what interactions were tested. This was not a process for testing all possible interactions; rather, only specific indicated effect modifications were tested.

Missing data were evaluated to determine if the pattern was missing completely at random (MCAR) or missing at random (MAR). If missing data were MAR or MCAR, SEM techniques were used to estimate missing values using either full information maximum likelihood or multiple imputation. If missing data did not fit an MAR or MCAR pattern, other options were explored including pattern mixture models. To the extent possible, potential bias due to attrition and missing data over time were assessed. All analyses were conducted using Stata (version 15, StataCorp) or MPlus (version 7, Muthén & Muthén).

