**Figure 2 figure2:**
[figure not shown]
Flow diagram for establishing Consortium to Study Opioid Risks and Trends (CONSORT) criteria for opioid use.

A randomly selected group of patients meeting criteria for short-term use at day 90 were invited to participate in the study assessment. This group of patients was selected to be time-matched 1:1 to patients continuing to use opioids at day 90 (initial issue date ±2 weeks) Although it was not possible to accurately apply CONSORT criteria for short-term use until month 6 following issuance of the last prescription, the study assessment was performed at this time point to ensure that patients were captured in the earliest stages of short-term use. Because it was anticipated that the majority of the cohort would meet criteria for short-term use, it was not feasible to invite all patients to participate in the study assessment.

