#### Sample Size Estimates

Based on our preliminary work [3,9,57-62], we estimated the rate of episodic opioid use would be 20% and the estimated rate of long-term use would be 7%. This would yield approximately 200 (780 × .27 = 210.6) patients developing some form of UPOU at each site. The analysis for specific aim 1 involved examining a wide variety of predictors of UPOU rather than 1 specific exposure. As a result, the minimum detectable odds ratios across a range of sample sizes were calculated. Setting the power at 0.8 and α at .05 (2-tailed), a total sample size of 1200 (600 cases and 600 controls) allowed detection of an odds ratio of 1.38 with a predictor that had a prevalence of 0.5 in controls and zero correlation in exposure between cases and controls. The detectable odds ratio (OR) goes up as the correlation between cases and controls becomes positive (detectable OR=1.48 with *r*=0.3), and it also increases as the prevalence of the exposure in the control group increases (detectable OR=1.55 with *r*=0.3 and prevalence of exposure=0.7 in controls).

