#### Data Analysis Plan

The primary research question for specific aim 1 was to identify patient characteristics associated with UPOU. A case-control design was used with controls time matched to cases. The expectation was that multiple patient characteristics would be associated with UPOU. Descriptive statistics (means, medians, and ranges) were generated to compare cases and controls on all patient characteristics. Differences in patient characteristics between cases and controls were assessed using bivariate tests including the McNemar test for categorical variables and paired 2-tailed *t* tests (or Wilcoxon signed rank test, if needed) for continuous variables. The results of the bivariate analyses were used to select variables for conditional logistic regression analyses to regress UPOU on all variables identified as potentially associated with the UPOU. The regression models were constructed in stages by incorporating predictors in conceptual blocks and using standard selection methods to retain variables. All models included a fixed effect for site. ORs and 95% CI were used to evaluate the magnitude and statistical significance of the association between predictors and outcome.

### Specific Aim 2

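### The Aim 3 structural equation models use date-matched cases and controls but, as described, carry no term for the matching date; the effect runs from nil to about 11–12 points of power, depending on within-pair correlation

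*Protocol article*

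**What the plan says.** Control selection is described below Figure 2 of the protocol article, in the Aim 1 timeline section. Patients classed as short-term users at day 90 were drawn at random: "This group of patients was selected to be time-matched 1:1 to patients continuing to use opioids at day 90 (initial issue date ±2 weeks". Date is the only matching factor named.

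The Aim 1 Data Analysis Plan follows this through: "A case-control design was used with controls time matched to cases", with McNemar tests, paired t or signed-rank tests, and conditional logistic regression with a fixed site effect. The Aim 2 Data Analysis Plan repeats these methods.

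Aim 1 Sample Size Estimates takes 600 cases and 600 controls and gives a detectable "odds ratio of 1.38 with a predictor that had a prevalence of 0.5 in controls and zero correlation in exposure between cases and controls". It then shows how the figure rises if exposures are correlated within pairs: 1.48 at r = 0.3, and 1.55 at r = 0.3 with control prevalence 0.7.

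Under Aim 3, SEM Analysis says: "The primary outcome measure was UPOU, measured as a dichotomous variable of cases and time-matched controls". The dependence it names is patients grouped by clinician and clinicians by site. Of the integrated model it says: "This involved multilevel SEM with a patient-level outcome (eg, UPOU) and predictors at the patient level, the clinician level, and the practice environment level". Aim 3 Sample Size Estimates counts 1200 patients nested in clinicians and practice environments. None of these places mentions the pair or the issue date.

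**The concern.** Matching forces cases and controls to have the same distribution of issue dates. A predictor that drifts with calendar time is then alike within pairs. A model of case status that omits the date estimates a marginal association, which lies closer to the null than the within-date association, and its ordinary standard errors are too large for the difference being tested.

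Drift over time is plausible. The Results section dates the start of recruitment to August 2019, reports a four-month halt in 2020, and describes later interruptions that differed by site.

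Three things are at stake:

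- Domain models are trimmed from a saturated model by information criteria and RMSEA, and attenuated paths are easier to trim away.
- Estimates from the claims database are to be compared with the clinical ones, so any shrinkage enters the benchmark.
- Aims 1 and 3 could differ on one predictor only because one analysis respects the matching. The article puts such differences down to latent variables and a change of model.

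**Working it through.** **Inputs.** From Aim 1 Sample Size Estimates: 600 pairs, two-sided α 0.05, power 0.80, and three sets of control prevalence p0, within-pair correlation r and OR. The results at r = 0.1 and 0.2 interpolate between the plan's two values of r. A single observed binary predictor stands in for an SEM path.

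**Pair table.** Let p1 be exposure prevalence in cases and c = r·√[p1(1−p1)p0(1−p0)]. The discordant probabilities are p10 = p1(1−p0) − c and p01 = (1−p1)p0 − c. Solve for p1 so that p10/p01 equals the OR. Put d = p1 − p0.

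- Matched power = Φ{[d√n − 1.96√(p10+p01)] / √(p10+p01−d²)}
- Power ignoring the matching = Φ{[d√n − 1.96√(2p̄(1−p̄))] / √(p10+p01−d²)}, with p̄ the mean of p1 and p0
- OR ignoring the matching = p1(1−p0) / [(1−p1)p0]

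**The plan's own figures.** With 600 pairs and 80% power the matched method gives detectable ORs of 1.385, 1.477 and 1.552, against the stated 1.38, 1.48 and 1.55. They reproduce.

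**Worked case: p0 = 0.5, r = 0.3, OR 1.48.**

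- p1 = 0.5680 and c = 0.3 × √(0.5680 × 0.4320 × 0.25) = 0.0743.
- p10 = 0.2840 − 0.0743 = 0.2097; p01 = 0.2160 − 0.0743 = 0.1417; ratio 1.48.
- d√600 = 0.0680 × 24.49 = 1.666, and √(0.3514 − 0.0046) = 0.589.
- Matched: (1.666 − 1.96 × 0.593)/0.589 = 0.86, power 80.4%.
- Ignoring the matching: (1.666 − 1.96 × 0.705)/0.589 = 0.48, power 68.5%.
- OR ignoring the matching: 0.5680/0.4320 = 1.315, about 1.32.
- Type I error ignoring the matching: 2[1 − Φ(1.96/√0.7)] = 1.9%.

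A simulation of 200,000 data sets gave 80.5% and 69.4% power, and 2.1% type I error.

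**Range, 600 pairs, by formula.**

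| p0 | r | Matched OR | OR ignoring matching | Matched power | Power ignoring matching |
|---|---|---|---|---|---|
| 0.5 | 0 | 1.38 | 1.38 | 79% | 79% |
| 0.5 | 0.1 | 1.42 | 1.37 | 82% | 79% |
| 0.5 | 0.2 | 1.45 | 1.35 | 81% | 75% |
| 0.5 | 0.3 | 1.48 | 1.32 | 80% | 68–69% |
| 0.7 | 0.3 | 1.55 | 1.36 | 80% | 68% |

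Table 1 reports 513 cases and 517 controls, so at most 513 pairs. With 513 pairs, p0 = 0.5, r = 0.3 and OR 1.48, power is 74% matched and about 60% ignoring the matching.

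**Does adjusting for date repair it?** In a simulation with a continuous predictor, 600 pairs and a correlation of 0.3 arising from calendar quarter (600 trials for power, 1,000 for type I error):

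| Analysis | Power | Type I error |
|---|---|---|
| Logistic, no date term | 67% | 1.6% |
| Logistic with calendar quarter | 78% | 4.4% |
| Paired test | 77% | 4.4% |

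A separate simulation gave 66% rising to 79%, and found no power cost of the date term at zero correlation.

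**The case against.** **The article is condensed, and nowhere says that the pairs are ignored.** A reader might infer that Aim 3 deliberately treats the patients as unmatched. The documents do not show that, and a date covariate could sit in a fuller plan. What remains is that the article describes the Aim 3 structure in three places and leaves out the one dependence its sampling created, while Aims 1 and 2 state their matched methods. The finding is therefore conditional: if fitted as described.

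**The plan does not assume r = 0.3.** A reader might take the 11–12 points as the plan's own expectation. The 1200 patients are tied to OR 1.38 at zero correlation, where nothing is lost; 0.3 is an illustrative scenario. If the correlation comes only from the date, 0.3 means that date explains about 30% of a predictor's variance. That is a lot for age, sex or employment. This objection stands in full.

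**Aim 3 is sized on another scale.** It quotes 0.13 SD at n = 500, close to (1.96 + 0.84)/√500 = 0.125 for a standardized coefficient. On that basis 0.13 at n = 1200 gives z = 0.13 × √1200 = 4.5, so power is ample. The power figures above are thus not a shortfall against Aim 3's stated target, and they transfer to a latent-variable model only by analogy. The bias toward the null does not depend on that sizing.

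**Site, false positives and Aim 1.** A reader might infer that site is neglected because the fixed effect is stated only for Aims 1 and 2, but the Aim 3 nesting names site. Nor are false positives inflated; the error is conservative. The matched Aim 1 results also inform the patient-domain model, which lowers the risk of dropping a real predictor without removing it.

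**Conclusion.** The point holds in a limited form. As described, the Aim 3 models do not carry the matching variable, although the design matched on it and the other two aims analyse accordingly. Fitted that way, paths for predictors that vary with issue date shrink toward the null and are tested conservatively.

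The loss is nil at r = 0, about 3 points of power at r = 0.1, and 11–12 points at r = 0.3. This rests on 600 pairs, one binary predictor as a proxy for an SEM path, and an r that the article does not report and that date-only matching may keep small. It does not invalidate Aim 3. It is worth correcting because the remedy is nearly free whichever value of r applies.

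**What to change.** In SEM Analysis, state that initial issue date, as calendar-quarter indicators or a spline, enters as a covariate of UPOU and of the predictors in each domain-specific model and in the integrated model. Keep site in these models, as the stated nesting implies.

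Standard errors clustered on the matched set need not be required. They correct the variance but leave the attenuated estimate as it is, and pairs cut across clinicians in the multilevel model.

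The cost is a sentence or two of text and a few degrees of freedom. The issue date is already recorded because it was used for matching, and the Results section reports that the SEMs are not yet finished.

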#### Sample Size Estimates

Common algorithms do not exist for assessing power for complex SEM; however, 3 aspects of sample size were considered. First, because of the iterative and complex nature of SEMs, it was important to verify that the sample size was sufficiently large to produce stable model estimates. There are simulation studies suggesting that for models of the size and complexity proposed, minimum sample sizes for model stability would likely be in the hundreds [64]. Second, comparing models requires a certain sample size. Published estimates of model degrees of freedom suggest that sample sizes in the hundreds would be sufficient to discriminate competing models [64]. Finally, given a set sample size, an expected detectable effect size was estimated. Setting statistical significance at =.05 (2-sided tests) and power at 80%, a sample size of 500, for example, would allow detection effects of approximately 0.13 SD units across time (ie, considered a small effect). Even accounting for losses due to missing data, which can become an issue when combining multiple sources of data at multiple levels, the proposed sample size of 1200 patients, and the smaller number of clinician and practice environments in which they were nested, should be sufficient to estimate stable, comprehensive models and detect relatively small associations between constructs.

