#### Clinician Recruitment

A total of 148 clinicians completed the CAOS survey. The Mayo Clinic site recruited 146 (98.6%) clinicians, and 2 (1.4%) clinicians were recruited at the University of Michigan site. Recruitment of unique clinicians at the Mayo Clinic site was limited, in part, by clinicians who prescribed opioids to more than 1 patient. Due to unanticipated administrative barriers at Yale University, no clinicians were recruited at this site. The data analysis of clinician characteristics associated with UPOU has been completed and the manuscript is under active development.

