## Discussion

### Principal Findings

The anticipated results of this prospective, case-control study should provide ample data to understand how patient, clinician, and practice environment characteristics facilitate or impede development of UPOU. More specifically, multivariate logistic regression models will elucidate the individual influence of each domain (eg, patient, clinician, and practice environment) on UPOU and multilevel SEMs will provide an estimate of latent variables and test associations at and across these different levels for categorical and continuous outcomes. Widespread dissemination will be facilitated by the results derived from the broader analysis of the OLDW.

The results of this study will further build existing knowledge about the clinical characteristics associated with UPOU. For example, in a systematic review and meta-analysis of 33 studies comprised of 1,922,743 individuals, patient-level characteristics associated with UPOU after surgery included female sex; high school level education; previous mental health diagnosis of depression, anxiety, or posttraumatic stress disorder; cocaine or alcohol use disorder; tobacco use; and preoperative use of prescription opioids, antidepressants, benzodiazepines, or antipsychotic medications [67]. In addition, a history of back and neck pain, fibromyalgia, and migraine headache were associated with UPOU after surgery [67]. However, interpretation of these findings was limited by varying definitions opioid naivety and UPOU, clinical and statistical heterogeneity, and varying approaches for establishing baseline clinical characteristics. The imprecision of the meta-analysis was due, in part, to the use of large administrative and insurance claims data by studies included in the systematic review, which limited the number of studies that were available for inclusion in the subgroup analysis of patient characteristics. The results of our study will extend these findings by including surgical and nonsurgical patients and using uniform definitions of opioid naivety and UPOU. Finally, due to imprecision associated with establishing previous psychiatric diagnoses [68,69], the severity of current depressive symptoms, the presence of positive and negative affect, and the level of pain catastrophizing were included as study outcomes.

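### The aim 3 missing-data rule makes pattern-mixture models depend on rejecting MAR, which observed data cannot do, and does not say how patients at a site with no surveyed clinicians are handled

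*Protocol article*

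**What the plan says.** The rule is in the protocol article, Specific Aim 3, SEM Analysis. It has three steps.

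1. The missing-data pattern is evaluated to decide whether it is MCAR or MAR.
2. "If missing data were MAR or MCAR, SEM techniques were used to estimate missing values using either full information maximum likelihood or multiple imputation".
3. "If missing data did not fit an MAR or MCAR pattern, other options were explored including pattern mixture models".

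One general safeguard follows: "To the extent possible, potential bias due to attrition and missing data over time were assessed".

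The model that this rule serves needs data from all three domains: "This involved multilevel SEM with a patient-level outcome (eg, UPOU) and predictors at the patient level, the clinician level, and the practice environment level". The aim 3 Sample Size Estimates section foresees "losses due to missing data, which can become an issue when combining multiple sources of data at multiple levels", and still regards the planned 1200 patients as sufficient.

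The Results section, under Clinician Recruitment, reports 148 completed surveys: 146 at Mayo and 2 at Michigan. On the third site it says: "Due to unanticipated administrative barriers at Yale University, no clinicians were recruited at this site". Table 1 lists 147 Yale patients. The Principal Findings section nevertheless expects that the study "should provide ample data to understand how patient, clinician, and practice environment characteristics facilitate or impede development of UPOU".

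**The concern.** MAR and missing not at random differ only in how missingness relates to values that nobody has seen. A rule that holds pattern-mixture models back until MAR has been shown not to fit waits for evidence that the observed data cannot supply. Once MAR is accepted, its results would stand without any described check on departures from it.

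The clinician survey is where this matters most. It measures attitudes and beliefs about opioids, so response that depends on those attitudes is plausible, although the documents do not show it. The aim 2 sample size section expected only 35% to 65% of clinicians to respond.

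The achieved data add a second difficulty. At Yale the whole set of survey-based clinician and practice variables is absent. If Yale patients stay in the integrated model under the stated likelihood or imputation route, the clinician and practice paths would seem to draw on three sites while resting almost wholly on one.

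**Working it through.** **1. The article's own figures.** From Table 1 and Clinician Recruitment:

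- Patients: 855 + 28 + 147 = 1030. Cases: 422 + 15 + 76 = 513. Controls: 433 + 13 + 71 = 517.
- Yale share of patients: 147/1030 = 14.3%.
- Mayo share of surveyed clinicians: 146/148 = 98.6%. Michigan: 2/148 = 1.4%. Yale: 0.

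All of these agree with the article.

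**2. Whether the trigger can be applied.** Take a binary clinician trait, and let r be the share of patients whose clinician data are observed. In each group the full-data prevalence is

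p = r × p(observed) + (1 − r) × p(unobserved).

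The data fix r and p(observed) but say nothing about p(unobserved). MAR given case status sets p(unobserved) = p(observed). A pattern-mixture model sets p(unobserved) = p(observed) + delta.

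The following inputs are assumptions for illustration, not figures from the article: r = 0.60 in both groups, and an observed prevalence of 0.50 in cases and 0.40 in controls.

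| Delta in cases | Delta in controls | p in cases | p in controls | Odds ratio |
|---|---|---|---|---|
| 0 (MAR) | 0 (MAR) | 0.50 | 0.40 | 1.50 |
| +0.10 | 0 | 0.54 | 0.40 | 1.76 |
| −0.10 | 0 | 0.46 | 0.40 | 1.28 |
| +0.10 | −0.10 | 0.54 | 0.36 | 2.09 |
| −0.10 | +0.10 | 0.46 | 0.44 | 1.08 |

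For the fourth row: 0.6 × 0.50 + 0.4 × 0.60 = 0.54; 0.6 × 0.40 + 0.4 × 0.30 = 0.36; (0.54/0.46)/(0.36/0.64) = 2.09.

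The observed data are the same in all five rows, so no evaluation of them can tell the first row from the others. A comparison of patients with and without missing values on other observed variables can speak against MCAR, and it can go no further.

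**3. What the rule implies for Yale.** Missingness of survey data at Yale is explained entirely by site, which is an observed variable. Under the written rule it could readily be classed as MAR and sent to full information maximum likelihood or multiple imputation. But with 0 surveyed Yale clinicians, the Yale distribution of these variables is not identified. Either method would have to assume that Yale clinicians resemble the pool of 148, of whom 98.6% are at Mayo. Full information maximum likelihood does not fill in values, but it relies on the same estimated relations. The Study Settings section describes the sites as different by design: a geographically defined population, surgical clinics, and a large delivery system. Practice environment is therefore a domain where this assumption is hard to defend.

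**4. How many patients could support the clinician paths.**

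- Sites with any surveyed clinician: at most 855 + 28 = 883 of 1030 (85.7%), with 422 + 15 = 437 cases and 433 + 13 = 446 controls.
- Mayo alone: at most 855 of 1030 (83.0%).

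Both are upper bounds, because the article does not report how many patients had a surveyed prescriber within a site. At clinician level, 148 is 36% of the lower planned number (148/410) and 19% of the upper (148/760).

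**The case against.** Five points can be made for the article.

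- **The text says evaluated, not tested.** Investigators may judge on subject-matter grounds that data are missing not at random and then turn to pattern-mixture models. This stands to a degree: a reader might infer that such models would never be run, and that goes too far. What remains is that the trigger has no evidential basis, and nothing is described for the case where MAR is accepted.
- **Bias from attrition and missing data over time is to be assessed.** That sentence is in the same paragraph and counts for something. It is unspecific, however, and its subject is loss over time. The clinician survey is completed once, so nonresponse to it is not clearly covered.
- **Nothing says that Yale clinician data are imputed.** This stands. A reader might infer that Mayo clinician data are carried over to Yale patients, but the article neither says so nor excludes it. The mention of losses when sources are combined fits patients dropping out of the linked model just as well, and the SEMs were still under development. The Yale point is therefore conditional.
- **The Yale gap had an administrative cause.** This also stands. The 14.3% measures a recruitment failure and is not evidence of attitude-driven nonresponse. Nor can Michigan's 28 patients simply be added to reach 175 without clinician data: two Michigan prescribers responded, and the number of patients linked to them is not given.
- **The imbalance is disclosed.** The Limitations section acknowledges it for patients and clinicians, notes limited generalizability, and rules out site-specific analyses for Yale and Michigan. So a reader should not infer concealment. The section does not, however, draw the consequence that the clinician and practice domains are essentially single-site, and Principal Findings makes no such reservation.

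**Conclusion.** The missing-data rule is badly fixed. It makes the not-MAR analysis conditional on a finding that observed data cannot deliver, and it describes no such analysis when MAR is accepted. This part rests on no numerical assumption. The odds ratio range of 1.08 to 2.09 around 1.50 only illustrates it, under the assumed inputs shown, and is not an estimate of bias in this study.

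The site point holds conditionally. If the stated likelihood or imputation route were applied to clinician and practice variables for the 147 Yale patients (14.3%), those results would rest on a clinician pool that is 98.6% Mayo. The article does not say whether this is done. The shortfall in surveyed clinicians was reported after the rule was set, so the point is that the published rule was not adapted to the data obtained. Since the SEMs were still being developed, the correction should be made before the integrated model is reported.

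**What to change.** - State MAR as an assumption for the primary SEM analysis, not as a finding, and keep full information maximum likelihood or multiple imputation under it.
- Run a delta-adjusted pattern-mixture sensitivity analysis whatever the missing-data evaluation shows, including for nonresponse to the clinician survey.
- Fit the clinician and practice paths only on patients whose prescriber was surveyed, and report that number by site and by case status.
- Describe those paths as essentially single-site (Mayo) results wherever the integrated model is reported, and qualify the statement in Principal Findings to match.

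The cost is revised wording, one extra analysis, and wider intervals for the clinician paths, which can draw on at most 883 patients and possibly far fewer. No new data are needed.
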